## Procedures

According to the national and regional indications, patients enrolled in this study will be vaccinated with either the Pfizer/BioNTech or with Moderna vaccines. Patients will be monitored for antibodies and cellular immunity directed against the SARS-CoV-2 spike antigen for 12 months or until death. In particular, blood samples for immunological testing will be performed at 6 time points (**Figure 2**) as follows: T0, the day of vaccination; T1, the day of the booster dose (according to the schedule of the vaccines: 3 weeks after T0 for patients receiving Pfizer/BioNTech vaccine, 4 weeks after T0 for patients receiving Moderna vaccine); T2, between 5 and 7 weeks after T0 for patients receiving Pfizer/BioNTech vaccine and between 6 and 8 weeks after T0 for patients receiving Moderna vaccine; T3, 12 (± 1) weeks after T0; T4, 24 (± 2) weeks after T0; T5, 52 (± 2) weeks after T0.

**Figure 2 f2:**
[figure not shown]
Schematic representation of the timeline of immunomonitoring of the clinical study.

## Immunological Efficacy Assessment

Humoral response: For each time point the humoral immune response to vaccination will be assessed by a serological assay able to detect anti-Spike IgG antibodies in sera Possible natural infection before or after vaccination will be assessed by measuring anti-Nucleocapsid IgG antibodies. Patients with potential concurrent SARS-CoV-2 infection identified through anti-N increased level at the same time point will be excluded by this analysis. On a subset of subjects, at 2-4 weeks after the booster dose and at 12, 24 weeks after first vaccine administration, a neutralization assay will be performed to evaluate the functional activity of vaccination induced anti-Spike antibodies. Briefly, sera from patients will be tested for their ability to neutralize SARS-CoV-2 infection of VERO-E6 cells in a BSL-3 facility.

T cell immunity: The cell-mediated immune response to vaccination will be assessed by a first-line test standardized on whole blood assay. Briefly, at the laboratory of each clinical center heparin blood samples will be stimulated in the absence/presence of a pool of peptides spanning the S protein (S: PepTivator^®^ SARS-CoV-2 ProtS, PepTivator^®^ SARS-CoV-2 ProtS1; PepTivator^®^ SARS-CoV-2 ProtS+, purchased by Miltenyi Biotech) for 20 hours at 37°C 5%CO2. The day after, conditioned plasma will be harvested and stored to quantify the release of IFNγ, TNFα, IL-2 and IP-10 cytokines by automated Immunoassay assay (Protein Simle, Biotechne). Moreover, peripheral blood mononuclear cells (PBMC) will be isolated and stored to allow subsequent other T cell assay (e.g., ELISpot assay).

All serological assays, quantification of released cytokines in conditioned plasma and ELISpot assay will be centralized in the Spallanzani laboratory to generate homogeneous data by sharing reagents and technologies.

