## Objectives

In the context of the national vaccination campaign in which available vaccines are administered to fragile patients, this study would like to assess prospectively the effectiveness of the COVID-19 vaccination in these specific subgroups, and to characterize the kinetics of the immune response to the vaccination and its persistence overtime. Here we have gathered together 12 healthcare centers recognized as centers of excellence by the Italian Ministry of Health (Istituti di Ricovero e Cura a Carattere Scientifico, IRCCS) to share one common protocol of vaccine assessment that has centralized the testing of antibody responses, and their neutralizing activities, and has shared common reagents and technologies for the evaluation of the T cell response to the Spike vaccine protein (**Figure 1**). Hopefully, the characterization of the subgroup responses will allow to shade some light on the true efficacy of the COVID-19 vaccination in the so called altered immunocompetent population.

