## Statistical Analysis

Descriptive analyses will be carried out and include statistics such as arithmetic mean, median and geometric mean, with corresponding 95% CIs for continuous outcomes generated by the immunological tests at each time point (at first dose, at second dose, 2 weeks after the second dose, at 3, 6 and 12 months after first vaccine administration). Percentages with corresponding 95% CIs will be computed to describe the frequency of COVID-19 infection and to report adverse events.

Analyses at specific time-points will be considered as well as a repeated measurements ANOVA will be implemented to study the trend over time in each subgroup with respect to subjects without evidence of considered diseases.

Analyses will be carried out overall and within each subgroup (underlying conditions and referents) to point out differences related to the specific condition. Sub-group analyses will be performed also for socio-demographic subgroups and comorbidities according to the consistency and other relevant variables of each subgroup. No missing data imputations is planned.

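### Dropping patients flagged by raised anti-N makes the late anti-Spike means depend on a post-vaccination event that may be linked to response; their earlier titres should stay in a mixed model

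*Protocol article*

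**What the plan says.** Under Immunological Efficacy Assessment (humoral response), anti-Nucleocapsid IgG is the infection marker: "Possible natural infection before or after vaccination will be assessed by measuring anti-Nucleocapsid IgG antibodies". The rule that follows is: "Patients with potential concurrent SARS-CoV-2 infection identified through anti-N increased level at the same time point will be excluded by this analysis". The article does not say whether a patient flagged at one visit comes back at later visits.

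Statistical Analysis plans arithmetic and geometric means with 95% CIs at each time point, and adds that "a repeated measurements ANOVA will be implemented to study the trend over time in each subgroup", compared with subjects without the diseases studied. It also states: "No missing data imputations is planned". The frequency of COVID-19 infection is to be reported separately.

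Objectives include the aim to "characterize the kinetics of the immune response to the vaccination and its persistence overtime". Procedures sets six sampling points, the last (T5) at 52 weeks.

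**The concern.** Titres measured after infection are not vaccine response, and keeping them out is right. The difficulty is the method. The flagged patient is removed and the remaining patients are summarised as if they stood for the whole group. The trigger is an event after vaccination that may depend on the quantity being measured. If patients with little vaccine antibody are infected more often, those left at T3 to T5 are a selected, better-responding set. The per-visit mean then answers how high titres are among patients not flagged, rather than how well the vaccine response lasts in the group.

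The geometric mean at late visits and its comparison with controls are at stake. Expected Outcomes says that related sub-analyses may inform who needs a third dose. A repeated-measures ANOVA that uses complete series only would also discard the flagged patient's valid earlier titres. The article does not say how that model treats incomplete series.

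**Working it through.** **1. The plan's own figure.** Sample Size gives a geometric mean of 286 AU/ml (95% CI 250 to 328, n = 250), a log SD of 1, 100 patients per subgroup, and a detectable difference of about 80 AU/ml at 80% power and 5% significance (taken as two-sided). With the 300 controls, the detectable log difference is 2.80 × 1 × √(1/100 + 1/300) = 0.3235, and 286 × (1 − e^−0.3235) = 79.0 AU/ml. With 250 controls it is 80.7. The figure reproduces, and in relative terms it is 80/286 = 28%. The quoted CI implies a log SD of ln(328/250)/(2 × 1.96) × √250 = 1.10, close to the stated 1.

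**2. Assumptions not in the document.**
- Infection before T5 follows a logistic model on the T4 log titre, with odds ratio 0.6 to 0.8 per natural-log unit.
- 5, 10 or 20% are infected.
- The T4–T5 correlation is 0.85, with equal SDs.

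**3. Selection effect with every infection flagged.** For a normal log titre with SD σ, slope b = ln(OR), infection probability p(X) with mean p̄, and correlation ρ:

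ratio of retained to true T5 geometric mean = exp{ρ |b| σ² E[p(X)(1 − p(X))] / (1 − p̄)}

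Example with σ = 1, OR 0.6 and 10% infected: 0.85 × 0.511 × 0.0878 / 0.90 = 0.0424, giving a ratio of 1.043. For σ = 1:

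| Infected | OR 0.8 | OR 0.6 |
|---|---|---|
| 5% | 1.010 | 1.022 |
| 10% | 1.019 | 1.043 |
| 20% | 1.038 | 1.087 |

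This is about 1 to 9% too high. If infection is unrelated to titre (b = 0), the ratio is 1.00. The effect grows with σ²: at an assumed SD of 2 it is 1.08 to 1.17 at 10% infected and 1.16 to 1.35 at 20%.

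**4. Selection effect when detection depends on response.** Let c be the logit slope of anti-N detection per SD of log titre and s the detection probability at the mean titre. At σ = 1, the probability of being flagged rises or falls with titre near the mean according to the sign of b(1 − p) + c(1 − s). With p = 0.10, s = 0.60 and c = 1:
- OR 0.6: −0.511 × 0.90 + 0.40 = −0.06, almost no selection.
- OR 0.8: −0.223 × 0.90 + 0.40 = +0.20, selection reversed.

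Over slopes of 1 to 2 and 5 to 20% infected, the ratio runs from 0.96 to 1.00 at SD 1 and from about 0.95 to 1.05 at SD 2.

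**5. Ranking between groups.** Take a weak group 1.5 SD below a strong one, with equal exposure, SD 1, 10% infected in the strong group, and infection probability 1 − exp(−L·exp(−b·x)). The ratios are:

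| Slope b | Detection in weak group | Weak | Strong |
|---|---|---|---|
| 0.5 | 100% | 1.112 | 1.053 |
| 0.5 | 59% | 1.059 | 1.053 |
| 0.25 | 100% | 1.039 | 1.027 |
| 0.25 | 59% | 1.021 | 1.027 |

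The 59% is the Introduction's seroconversion figure after infection under anti-CD20 therapy. It is only a proxy, because the antigen is not given. With it, the ranking nearly disappears or reverses.

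**6. Would leaving infected patients in be better?** No. With an assumed rise of 1.5 log units after infection and 2 to 20% infected, unadjusted inclusion overstates the geometric mean by factors of 1.03 to 1.35. That was worse than exclusion with full detection in every case run.

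**The case against.** - **The flag is itself an antibody test.** The Introduction reports seroconversion after infection of 82% in haematological malignancy, 59% under anti-CD20 therapy and 60% after stem cell transplantation. The weakest responders may go unflagged and stay in. This stands, and it removes any firm claim about direction.
- **The size rests on assumptions.** The document gives no infection rate, no titre–infection relation and no SD above about 1.1. A reader might infer that patient/control ratios are inflated by 5 to 33%, close to or beyond the 28% detectable difference, and most in the weakest-responding groups. The document does not support that. The upper figures need an SD of 2 with 20% infected, full detection, and less infection among controls. The controls are health care providers, whose exposure may be as high or higher.
- **The wording may mean visit-level omission.** The rule refers to the same time point, so earlier titres may be kept, and ruling out imputation does not rule out a likelihood fit. This is fair. Even so, the planned per-visit means lose the flagged value and borrow nothing from that patient's earlier ones.
- **Estimator detail may sit in a fuller plan.** That holds for model specification. The exclusion, the per-visit means and the absence of imputation are stated choices, however, and the point concerns those.
- **The remedy is not perfect.** Its residual bias is at most about 0.5% if infection depends on the observed T4 titre. If infection follows a later, unobserved titre (SD 2, full detection), about 1 to 11% remains, against 8 to 42% unadjusted. It is better than the planned estimate but not free of bias.

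**Conclusion.** The point holds in a limited form. The stated rule conditions the T3 to T5 anti-Spike means on a post-vaccination event that may depend on response, while persistence is an objective. Overstatement follows only if infection is likelier at low titre and anti-N detects it about equally at all response levels. It is then about 1 to 9% at the plan's log SD of 1, under the assumed odds ratios of 0.6 to 0.8 and 5 to 20% infected, and larger if titres are more spread out. With detection that falls as response weakens, the bias may be nil or reversed.

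For scale, the 95% CI of a 200-patient group at SD 1 is exp(±1.96/√200), or −13% to +15%. The bias at SD 1 is smaller than that but does not shrink with more patients. The document does not establish the direction of the bias or which group is most affected. The sample size figure is unaffected.

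**What to change.** Keep post-infection titres out, but keep the patient:
- Set anti-Spike titres to missing from the first flagged visit onward, and retain all earlier titres.
- Estimate geometric means at each visit, by disease group and in controls, from a likelihood-based mixed model on log titre. This replaces complete-case per-visit means, or a repeated-measures ANOVA that drops incomplete series, as the basis for inference. It needs no imputation.
- Report these beside the observed means, with the number flagged and the last pre-infection titre of flagged and unflagged patients, by group and visit.
- Add a simple sensitivity analysis for departures from missing at random, for example shifting the predicted post-infection log titres over a stated range.

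The cost is analysis wording and one model on data already collected. The model assumes that titres are missing at random given the earlier ones. This is weaker than the assumption behind the observed means, that being flagged is unrelated to response. Some bias remains if infection follows waning between visits, and undetected infections are not corrected. The report should state both limits.

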## Study Design

The VAX4FRIAL study is an observational, multicentre, prospective study with the general objective is to assess the effectiveness of the COVID-19 vaccination in terms of induction of humoral and cell-mediated immune responses in selected fragile (altered immunocompetence) populations, due to their underlying conditions or therapeutic treatments. It will be conducted through the creation of a network between 12 IRCCS in Italy. The study will be carried out in compliance with the Helsinki Declaration. The protocol has been approved by national competent authorities (AIFA) and the ethics committee of National Institute for Infectious diseases Lazzaro Spallanzani (IRCCS), and has been registered in ClinicalTrials.gov (NCT04848493). All patients will sign written informed consent before being enrolled for the study. We also recommended that COVID-19 vaccination studies activated independently by each institution shared the same outline as VAX4FRAIL. This recommendation was made to allow for the possible pooling of data from eligible cases not originally included in the VAX4FRAIL study.

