## Exclusion Criteria

i) Patients with psychiatric illness/social situations that would limit compliance with study requirements; ii) History of laboratory-confirmed SARS-CoV-2 infection.

A hemogram will be performed for each patient before vaccination to evaluate the baseline levels of neutrophils, lymphocytes and monocytes. A control group of subjects without evidence of specific disease will consist of 300 Health Care Providers collected by IRCCS Spallanzani, Rome, receiving the same vaccination treatments, and assessed for humoral and cell-mediated immune responses with the same procedures of this protocol.

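### As naturally read, the anti-N infection exclusion covers the antibody analysis but not the Spike T-cell analysis of the same visit

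*Protocol article*

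**What the plan says.** The general objective in Study Design joins the two readouts: effectiveness is to be judged "in terms of induction of humoral and cell-mediated immune responses in selected fragile (altered immunocompetence) populations".

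The Immunological Efficacy Assessment section then has two labelled paragraphs.

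- **Humoral response.** Anti-Spike IgG is measured at each time point. On infection the paragraph says "Possible natural infection before or after vaccination will be assessed by measuring anti-Nucleocapsid IgG antibodies", and then "Patients with potential concurrent SARS-CoV-2 infection identified through anti-N increased level at the same time point will be excluded by this analysis". Neutralisation on a subset of subjects is described after that sentence.
- **T cell immunity.** "The cell-mediated immune response to vaccination will be assessed by a first-line test standardized on whole blood assay". Blood is "stimulated in the absence/presence of a pool of peptides spanning the S protein", and the cytokines released are quantified. Cells are also stored for further tests such as ELISpot. No infection rule appears here.

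Statistical Analysis describes summaries of the immunological outcomes at each time point and states no infection exclusion for either readout. It does plan to report how often COVID-19 infection occurs.

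Exclusion Criteria bars entry on "History of laboratory-confirmed SARS-CoV-2 infection". Procedures sets the follow-up: "Patients will be monitored for antibodies and cellular immunity directed against the SARS-CoV-2 spike antigen for 12 months or until death".

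**The concern.** The anti-N exclusion exists because an anti-Spike signal cannot by itself show whether the vaccine or the virus produced it. The T-cell test has the same problem, since it stimulates with Spike peptides and measures what is released. The reason for excluding infected patients therefore applies to both readouts, but the rule is attached to one.

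Two things are at stake. First, a T-cell result presented as response to vaccination would include responses due to infection. Second, at a given visit the antibody and T-cell results would describe partly different patients, although the objective treats them as two sides of one question in the same populations. The later visits, where persistence is judged, are the most exposed, because infections accumulate over follow-up.

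**Working it through.** **The plan's own figure.** The article gives no infection rate and no T-cell response rate. Its one design figure, a detectable difference of about 80 AU/ml with 100 patients per subgroup (Sample Size), concerns antibody titre. It reproduces against the 300 controls: (1.960 + 0.842) × 1 × √(1/100 + 1/300) = 0.3235 on the log scale, and 286 × (1 − e^−0.3235) = 79.0 AU/ml. The point does not rest on it.

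**Step 1: follow one patient through the text.** Take a patient with raised anti-N at the 24-week visit. The Humoral response paragraph removes the patient from the IgG summary of that visit. Nothing in the T-cell paragraph or in Statistical Analysis removes the same patient from the cytokine summary of that visit.

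**Step 2: can such patients occur?** The entry criterion removes only laboratory-confirmed earlier infection. Unrecognised earlier infection remains possible, and so does infection during the 12 months. The plan expects both, since it tests for infection before or after vaccination and intends to report its frequency.

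**Step 3: what the difference could do (assumed inputs).** Let q be the share of a subgroup with raised anti-N at a visit. Let k be the factor by which infection raises their cytokine release, and r the response rate due to vaccine alone.

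- Geometric mean: log GM = (1 − q)μ + q(μ + log k) = μ + q log k, so the geometric mean is multiplied by k^q.
- Response rate, if every infected patient responds: (1 − q)r + q.
- Patients in the T-cell summary but not in the antibody summary: q × n, for the planned subgroups of 200, 400 and 500.

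| | q = 5% | q = 10% | q = 20% |
|---|---|---|---|
| k^q, k = 3 | 1.056 | 1.116 | 1.246 |
| k^q, k = 10 | 1.122 | 1.259 | 1.585 |
| r = 20% reads as | 24% | 28% | 36% |
| r = 50% reads as | 52.5% | 55% | 60% |
| q × n (200 / 400 / 500) | 10 / 20 / 25 | 20 / 40 / 50 | 40 / 80 / 100 |

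The k^q rows apply to the geometric mean only. The plan also reports arithmetic means, which would move by 1 + q(k − 1), for example 1.20 at k = 3 and q = 10%. It reports medians too, which are less sensitive to a small infected share.

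For a patient-to-control ratio of geometric means with a common k, the distortion is k^(q in patients − q in controls). It can go either way and vanishes if the two shares are equal.

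**Step 4: how clean is the antibody set?** The exclusion acts only on a raised level at the same visit, so a patient whose anti-N has fallen again re-enters later. It also needs the patient to seroconvert. The Introduction cites SARS-CoV-2 IgG seroconversion after infection of 82% in haematological malignancy and 59% under anti-CD20 therapy. If anti-N behaved alike (an assumption), 18% and 41% of infections would be missed. With a true infected share of 10%, the share left after exclusion would be 0.10 × 0.18 / (1 − 0.10 × 0.82) = 2.0% and 0.10 × 0.41 / (1 − 0.10 × 0.59) = 4.4%. The rule reduces contamination but does not remove it.

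**The case against.** The strongest reply is that no sentence says infected patients are kept in the T-cell analysis. The rule speaks of patients, not of titres, and its reference to the present analysis stands under a section heading that covers both assays. The article condenses a fuller protocol, and analysis sets by endpoint are commonly left to that protocol or to a SAP.

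Part of this stands. The wider reading is possible, and a reader should not infer that the sponsor chose to keep infected patients in the T-cell results. But the sentence sits inside the labelled Humoral response paragraph, directly after the IgG assay, so the narrow reading is the natural one. The point is not that a detail is absent. A rule is stated, and its stated place ties it to one of two readouts that both need it.

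Three further objections also have force:

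- A reader might infer that the antibody results are free of infection and only the T-cell results are affected. Step 4 shows otherwise. The asymmetry concerns detected infections only.
- A reader might infer that any pattern of weak antibodies with preserved T cells would be an artefact. The documents do not support that. The study is mainly descriptive, no comparison of discordance between the readouts is described, and third-dose questions are left to post-hoc work outside the objectives (Expected Outcomes).
- Different denominators are not a fault in themselves. Neutralisation is done on a subset by design. The fault is that the difference here depends on infection, which affects the outcome.

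**Conclusion.** The point holds with a limited claim. As naturally read, patients with detected infection leave the antibody results and remain in the Spike T-cell results of the same visit. Those T-cell results would then mix vaccine- and infection-induced responses, in a population partly different from that behind the antibody results.

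The size is unknown. It is likely small at early visits, because laboratory-confirmed earlier infection is excluded at entry, and larger at later ones. The table shows what given values of q and k would imply; neither comes from the documents, and no single entry should be quoted as the expected bias.

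The conclusion rests on the narrow reading of the rule. If the full protocol already extends it to T cells, that part is settled by saying so; the re-entry problem created by the same-visit wording would still need attention.

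**What to change.** State one infection rule, preferably in Statistical Analysis: the anti-N exclusion applies equally to anti-Spike IgG, neutralisation, whole-blood cytokines and ELISpot, in patients and in the Health Care Provider controls, from the first raised anti-N onward. The last part is needed because the current wording lets an infected patient return once anti-N falls. Add a sensitivity analysis that includes infected patients in all readouts.

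The cost is a few sentences and one extra analysis. Anti-N is already planned, so no new samples are required. There are two downsides. Slightly fewer T-cell samples will be available at late visits. And because anti-N misses infected patients who do not seroconvert, some contamination stays in both readouts and the exclusion falls selectively on patients able to make antibody. That should be stated as a limitation, especially for haematological malignancy and anti-CD20 therapy.
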